best possible outcome for PCWS in the daily clinical practice before the age of 6 years, so within the preschool age years (also called 'the window of opportunity').

We estimate, based on findings from the literature, that the three treatment programs will achieve similar outcome at 18 months post-randomisation. That is, (near) zero levels of stuttering and linked to this result, a high score on Quality-Of-Life scores (QOL), a positive attitude towards communication and no or low impact of stuttering on the preschool child and his parents. Currently, these three stuttering treatment approaches for preschool age children are delivered daily to Belgian preschool age children who stutter. Their effect compared to each other, however, is not known. We believe, as it is our duty to aim for as much recovery of early childhood stuttering as possible before stuttering becomes persistent, that the current trial is necessary to support current practice in Belgium. Also, it is essential to provide evidence for the treatments to help SLTs choose the most appropriate treatment approach for a family.

As a secondary objective, we expect a significant difference in treatment time necessary to reach the treatment goals. We believe that the direct treatment programs (the LP and Mini-KIDS) need less treatment time (measured in hours) than SCBT with a difference of about 1/3 to nearly 1/2 of the treatment time. This is an estimation based on available publications (Arnott et al., 2014; Bridgman et al., 2016; De Sonnevile-Koedoot et al., 2015; Donaghy et al., 2020). We believe that this is an important objective with implications on both the families and the Belgian reimbursement system. To shorten the treatment time implies a reduction of parents' burden of providing time and travelling to the stuttering practice and the costs for parents and the National Institute for Health and Disability Insurance.

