### 4.2 Secondary objectives

The secondary objectives are

- To compare the %SS, measured on video recordings by blinded video analysts, between PCWS treated with Mini-KIDS, SCBT and the LP at 3, 6, 9 and 12 months post-randomisation
- To compare the Severity Ratings (SR, a subjective measure for frequency and severity, measured on video recordings by blinded video analysts) between PCWS treated with Mini-KIDS, SCBT and the LP at 3, 6, 9, 12 and 18 months post-randomisation
- To compare the Quality of Life (QOL, measured with the EQ-5D-Y proxy 1) and the impact of stuttering on PCWS and parents (measured with the ISPP-questionnaire) between PCWS treated with Mini-KIDS, SCBT and the LP at 3, 9 and 18 months post-randomisation
- To compare parent report about stuttering severity and satisfaction with everyday communication between PCWS treated with Mini-KIDS, SCBT and the LP at 3, 6, 9, 12 and 18 months, 2 and 5 years post-randomisation
- To compare the communication attitude (measured with the KiddyCAT) between PCWS treated with Mini-KIDS, SCBT and the LP at 18 months post-randomisation
- To compare the %SS and SR (measured on video recordings by blinded video analysts) and QOL (EQ-5D-Y proxy 1) between PCWS treated with Mini-KIDS, SCBT and the LP at 2 and 5 years post-randomisation
- To compare the treatment time (in hours), number of weeks and number of treatment sessions until the start the maintenance phase of each treatment
- To look at the proportion of children that are successful (defined as  $<1$  %SS and  $SR \leq 1$ ) at 18 months and at 5 years post-randomisation.
- To evaluate %SS and SR at 18 months post-randomisation for the videos at home.
- To evaluate %SS and SR at 18 months post-randomisation for the videos recorded during the treatment sessions.

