### 9.1.5 Skill training

The goal of this phase is to train skills to use speech and language diversely to ask, to request, to explain, to make stories, to tell tales, to fantasize, ...

Conversation skills may also be introduced and practised such as taking turns (and waiting turns), speaking up, learning to interrupt, asking additional questions as well as listener skills such as giving feedback, giving attention or saying goodbye. The applied method is motivating the PCWS, modelling, concretising, associating neutral and positive emotions and applying skill training techniques.

Social conversation skills refer to verbal and non-verbal behaviour in interaction with other children and adults. Verbal behaviour includes language use and conversation skills. Non-verbal behaviour includes posture, gestures, eye contact and facial expression.

Training articulation skills is useful in young children who stutter severely, who have speech production skills below expectation and respond to the stuttering with irritation or frustration. The SLT mainly stimulates the PCWS and avoids direct interventions such as placing a tongue spatula. These skills include mobility with tongue and lips, sound imitation, strength and tension, diadochokinetic and sound-specific exercises.

Finally, variation of speech and voice lead to an increase of feelings of pleasure and being a competent speaker. These also create conditions in which the entire language and speech motor system becomes more flexible to make (unconscious) adjustments which can therefore also change the behavioural responses to stuttering (e.g. secondary behaviour, muscle tone...).

The PCWS can conclude the treatment phase and move to the maintenance phase when (1) the stuttering does not develop, (2) there is a reduction of stuttering severity during at least 3 to 4 months, (3) the PCWS developed a positive attitude towards his/her speech, (4) the PCWS is resilient towards stuttering-inducing factors and (5) the parent(s) provides a more stable and fluency-inducing behavioural model environment to the PCWS and deals independently and appropriately with the PCWS's stuttering.

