During Stage 1, treatment sessions are scheduled weekly. The sessions begin with a conversation between the parent (or the SLT) and the PCWS so that the SLT can record a SR (this can also be made based on a recording of the PCWS conversing during everyday life). The SLT then discusses the daily use of the SR-scale with the parent. They focus on stuttering severity and treatment responsiveness during the past week. The parent(s) then demonstrates to the SLT how verbal contingencies were given to the PCWS during the previous week (this can also be made based on a recording). The SLT determines if the parent(s) delivers them in an appropriate way and discusses them with the parent(s). If applicable, they discuss changes to the procedure for the coming week and the SLT models the new (or changed) procedure during an interaction with the PCWS. Then, the parent(s) demonstrates his/her delivering of the new (modified) verbal contingencies and the SLT gives feedback to the parent(s). The SLT concludes the session with a summary of the procedures to be applied for the coming week and discusses them with the parent(s).

Later on, the practice sessions, that the parent(s) implement at home with the PCWS, become more natural and resemble everyday conversations. Also later on in the treatment, a limited number of verbal contingencies are given throughout the day. When the PCWS has typical scores of 0 and 1 on the SR-scale with more 0s than 1s per week for three consecutive weeks, and the stuttering is rated as 0 or 1 during the treatment session, the PCWS can proceed to stage 2.

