- For the continuous measures SR, EQ-5D-Y proxy 1, measured at different time points we can compare the evolution over time between the programs using a linear mixed model. This model also allows to look at differences at a specific time point in a post-hoc comparison. For the answers to the ISPP-questionnaire measured at different time points this can be done using a generalized linear mixed model. For the ordinal outcomes parent report about their PCWS's stuttering severity and their satisfaction about the PCWS's communication in everyday speaking situations depending on variability a linear mixed or generalized linear mixed model will be used.
- The number of weeks, the number of treatment sessions, the treatment time needed until the maintenance phase begins will be compared between the three programs using an ANOVA or Kruskal Wallis test as appropriate. This outcome will also be studied in a multiple linear regression model adjusting for possible confounders.
- We will look at the proportion of children that are successful (defined as  $<1\%$  SS and  $SR \leq 1$ ) at 18 months and at 5 years post-randomisation. They will be compared by a Chi-square test (or Fisher's exact test as appropriate) between the three programs. The time to reach success between the three programs will be compared with a Kaplan-Meier plot and analyzed using a Cox regression model with correction for confounders.
- %SS and SR at 18 months post-randomisation will be evaluated separately for the videos at home and for the videos recorded during the treatment sessions using linear regression models as described for the averages of the two samples.
- For the above analysis we will first consider the intention-to-treat population to preserve randomization, if necessary also per-protocol population will be considered.
- Safety analysis will be done in all patients that are randomised.
- Numbers of children who drop out and reasons for drop out, as well as leave the allocated treatment arm (numbers, reason and switched treatment) will be described per treatment. Numbers per program will be compared using a Chi-square test (or Fisher's exact test as appropriate). A time to drop-out analysis or a time to switch analysis will be performed in case  $> 10\%$  drop-out or a 10% switch was present in the trial.

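### Treatment time to maintenance has no value for children who never reach maintenance, yet it is to be compared by ANOVA, Kruskal-Wallis and linear regression with intention-to-treat first

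*Protocol*

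**What the plan says.** Section 4.2 lists among the secondary objectives: "To compare the treatment time (in hours), number of weeks and number of treatment sessions until the start the maintenance phase of each treatment". Section 2 gives the expectation behind it, "we expect a significant difference in treatment time necessary to reach the treatment goals", and calls the objective important for families and for reimbursement.

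Section 11.3.3 fixes the method: "the treatment time needed until the maintenance phase begins will be compared between the three programs using an ANOVA or Kruskal Wallis test", as appropriate. It adds "This outcome will also be studied in a multiple linear regression model adjusting for possible confounders". For this and the neighbouring analyses, "we will first consider the intention-to-treat population to preserve randomization".

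The next item of the same section treats a parallel outcome differently: "The time to reach success between the three programs will be compared with a Kaplan-Meier plot and analyzed using a Cox regression model". Success there means below 1 %SS with SR of at most 1, the same for all arms.

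Maintenance entry is defined separately for each program:
- **LP (9.3.1):** severity ratings of 0 and 1, "with more 0s than 1s per week for three consecutive weeks", and 0 or 1 in the session.
- **SCBT (9.1.5):** five conditions, one being that "there is a reduction of stuttering severity during at least 3 to 4 months".
- **Mini-KIDS (9.2.5 and 9.2.6):** the Stage 4 goals, which include recovery or near-zero frequency over a long period that is not quantified.

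**The concern.** Time until an event is undefined for a child in whom the event is not observed. ANOVA, Kruskal-Wallis and ordinary regression need one finished value per child. Taken literally, the plan leaves two options. One is to leave non-reachers out, which conflicts with putting intention-to-treat first. The other is to enter their unfinished durations as if complete. In both cases a program under which fewer children reach maintenance need not look any slower.

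At stake is a secondary result to which the protocol attaches weight in section 2. The entry rules also differ by arm, so even a correct analysis measures time to each program's own goal, not time to one common level of fluency.

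**Working it through.** **1. Are non-reachers expected?** Yes, on the protocol's own text.
- Section 8.8.10 provides for a child who at 2 years is still being treated and is not in maintenance.
- Section 8.10.1 keeps children who leave the allocated arm in follow-up, possibly on other treatment.
- Section 11.1 assumes 11% dropout.
- Section 11.4.3 expects stuttering to persist in a small number of children.
- Section 11.4.2 expects maintained near-zero stuttering in 80% at 2 and 5 years. The other 20% is only a rough proxy, because maintained near-zero stuttering is not the same as entering maintenance.

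**2. Arm size.** The protocol gives no sample size or attainment rate for this outcome, so the arm size comes from the primary endpoint. With margin 1.0, SD 1.7, one-sided 1.25% and 90% power:

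n = 2 × (1.7/1.0)² × (2.2414 + 1.2816)² = 5.78 × 12.41 = 71.7, so 72 against the stated 73.

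73/0.89 = 82.02, so 83 per arm, and 3 × 83 = 249 as stated. Then 0.11 × 83 ≈ 9 dropouts per arm and 0.20 × 83 ≈ 17 by the proxy. The two groups may overlap.

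**3. Does another section supply a value?** Section 11.3.4 names last observation carried forward and multiple imputation for the primary outcome only. The mixed model it describes is for repeated measures. Neither gives a time to maintenance.

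**4. What an observed-value mean does (assumed inputs).** Take lognormal times, median 60 weeks, log-SD 0.6, cut at 104 weeks.
- z = ln(104/60)/0.6 = 0.917, so 82.0% of those who would ever reach maintenance do so by week 104.
- Mean among them: 60 × e^0.18 × Φ(0.917 − 0.6)/Φ(0.917) = 71.8 × 0.624/0.820 = 54.7 weeks.
- This is 54.7 whether 0% or 40% of the arm never reach maintenance, because non-reachers do not enter it.
- Restricted mean to 104 weeks in all children: 71.8 × 0.624 + 104 × 0.180 = 63.5 with 0% never reaching, and 0.6 × 63.5 + 0.4 × 104 = 79.7 with 40%.

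**5. Simulation (assumed inputs).** 83 per arm, lognormal times, 11% dropout spread evenly over the horizon, horizon 78 or 104 weeks, 1,500 trials per scenario, tests at 5%.

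| Scenario | Observed values only | All randomised, non-reachers ranked worst |
|---|---|---|
| Identical arms (median 40 weeks, 10% never reach) | about 5% | about 5% |
| Median 40 in all arms; 10/20/40% never reach; log-SD 0.5 to 0.8 | about 5% | 67% to 84% |
| Medians 40/52/80; 10% never reach; log-SD 0.8; 78 weeks | 62% | 98% |

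With medians 40/52/80 and log-SD 0.5, the untruncated means are 45.3/58.9/90.7 weeks, a slowest-to-fastest gap of 45.4. Observed-value means are 39.4/45.9/54.6 at 78 weeks (gap 15.2) and 42.4/51.6/65.5 at 104 weeks (gap 23.1). The test still rejects almost always there, but the estimated difference is a third to a half of the true one.

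**The case against.** **Nothing defines a completers-only set, and details go to a separate analysis plan.** Both are true. Kruskal-Wallis could rank non-reachers worst. But the protocol names the methods, two of them (ANOVA and linear regression) cannot use such a rank as a duration, and the Kaplan-Meier/Cox approach chosen for the parallel outcome is not used here. The restriction to reachers is a consequence of running the named methods on available values, not a stated rule.

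**Eighteen months was chosen so that all can complete treatment (4.3.1).** That is an intention, and 8.8.10 does not rely on it.

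**Failure would show elsewhere.** Section 11.3.3 also compares success proportions, time to success, dropout and switching. This stands as mitigation: a reader of the full report would not be blind. It does not make the treatment-time result itself right.

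**Entry rules.** A reader might set SCBT's 3 to 4 months (13 to 17 weeks) against LP's three weeks and conclude that 10 to 14 weeks of any difference is built into the definitions. The document does not support that. SCBT's period is one of reduction, which can run while treatment continues. LP's is a period at ratings of 0 to 1, after reduction has occurred. SCBT asks for no fixed near-zero level, so the net direction is open. Nor can the expected gap of 47 half-hour units (94 − 47) serve as denominator, because section 4.3.1 includes screening, parent and maintenance sessions in those totals. Timing each program's own goal is also the stated objective (sections 2 and 4.2), and a legitimate one.

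**Economics.** A reader might infer that the economic evaluation inherits the problem. Section 11.4.3 bases burden and cost on the number and length of sessions, not on this comparison.

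**Conclusion.** The point holds as a flaw of method in a secondary analysis. The named tests have no value for children whom the protocol itself expects. On observed values they describe only those who reached maintenance and understate durations. Differences between arms are missed or shrunk if attainment or duration differs by arm; with identical arms the type I error stays near 5%.

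A definite bias for or against one program would be a stronger reading, and it cannot be drawn. Attainment by arm, spread and calendar time to maintenance are assumptions in every figure above, and the 40% has no source in the protocol. The differing entry rules limit interpretation but are not shown to favour an arm. The primary %SS comparison, its sample size and the non-inferiority conclusion are untouched.

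**What to change.** Leave the clinical entry criteria as they are and change the analysis text in 11.3.3:

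1. **Weeks to maintenance:** Kaplan-Meier and Cox in all randomised children, as already planned for time to success, with children still in treatment censored at last contact. Because dropout may be informative, add a sensitivity analysis that ranks dropouts and other non-reachers worst.
2. **Hours and sessions to maintenance:** a rank test in all randomised children with non-reachers ranked worst. Accumulated hours make a poor survival time axis, since censoring then depends on treatment intensity.
3. **Report the proportion reaching maintenance in each arm** beside these results.
4. **State that the outcome is time to each program's own goal.** Neither Cox nor ranking cures the differing entry rules.
5. **Supportive analyses:** cumulative logged sessions and hours to 18 months, and the time to the common success criterion already in 11.3.3.

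Cost: slightly more analysis work. Date and duration of each session are already collected to 18 months (8.8.5 to 8.8.9). The weak spot is children who leave the allocated arm: section 8.10.1 lists videos and questionnaires for them but not session logs, so their cumulative totals may be incomplete and should be reported as such.

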#### *11.3.4 Procedure(s) to account for missing or spurious data*

Most of the data is routinely collected as standard of care and the SLT will be in contact with the PCWS regularly to ensure collection of all relevant data.

The SLT follows up on the missing data and records any reasons for missing data in PCWS' speech-language therapy files and the eCRF (REDCap).

For the sensitivity analysis of the primary outcome, we considered last observation carried forward, as an alternative we will also explore multiple imputation techniques and compare results.

The proposed linear mixed model allows that subjects have missing values at certain time points as the model uses all available data points per subject. The missing value assumption of the model is Missing At Random which means that missing values can only be dependent on the observed responses which seems a reasonable assumption in this case.

#### *11.3.5 Other statistical considerations.*

We will explore if we can find a profile of children more successful to one of the programs, possible factors that will be studied are gender, co-morbidities, age at assessment, family history of stuttering, family history of recovery of stuttering, onset data (gradual/sudden, time since onset, progress since onset), answers to the ISPP-questionnaire, baseline stuttering severity assessment (%SS and SR), parent profile and temperament (CBQ-short version). This will be studied in a linear regression model with %SS at 18 months as outcome and in a logistic regression model with success defined as  $<1\%$  SS and  $SR \leq 1$  as a binary outcome.

We will explore the agreement between the video samples recorded at home and those recorded during the sessions for %SS and SR.

### **11.4 Data collection for economic evaluation**

For the disorder of stuttering, 128 sessions of 30 minutes are being reimbursed by RIZIV-INAMI within a period of 2 years. For preschool age children, only sessions of 30 minutes are reimbursed. Of these 128 sessions, 10 can be provided to parents without the child, as sessions of 60 minutes. If treatment is finalised before using 128 sessions and the child relapses within 6 months to 2 years after treatment, which is common for this disorder, 38 sessions of 30 minutes can be provided within a period of 1 year. That is, until the 128 sessions are used.

These sessions are used for treatment and parent coaching. Of these sessions, the cost for RIZIV/INAMI and for the patient is calculated on the condition that the stuttering specialist is conventioned

(“geconventioneerd”, “met overeenkomst”) and that the patient does not have a preference scheme (“zonder voorkeursregeling”).

Important note: Independently of the results of this trial, we do not question the number of reimbursed treatment sessions in the existing reimbursement scheme. Older children and adults who stutter need more treatment over a long time. Also, stuttering is known to be a relapse-prone disorder.

|           | Total Time (in
Assessment +
Treatment of 30
minutes)* | Total cost (€) | Total R/I (€) | Total P (€) |
|-----------|----------------------------------------------------------------|----------------|---------------|-------------|
| LP Cost   | 47                                                             | 1264.7         | 1000.2        | 264.5       |
| Mini-KIDS | 61                                                             | 1642.6         | 1299.1        | 343.5       |
| SCBT      | 94                                                             | 2103.9         | 1660.9        | 443.0       |

\* Assessment time is not included in the 128 sessions

The calculations differ with previous calculations as we adapted the calculations to the set-up of the trial and added the data from the file audit (Mini-KIDS) and the most recent meta-analysis (Park et al., 2021). The calculations are based on assessment, six 60-minute treatment sessions and then 30-minute sessions.

Treating stuttering at preschool age is more successful, but also, once stuttering evolves to persisting stuttering, it can have a significant impact on the social activities of the person who stutters. It is known that adults who stutter have a 7-fold risk to developing anxiety disorders (Iverach et al., 2009). Hence, a person who (persistently) stutters costs the health system and the patient much more, given that psychological treatment may be necessary besides speech therapy.

#### 11.4.1 Burden

The number of patients affected by the intervention under study per year in Belgium is calculated based on incidence numbers in the literature. Between 8% to 11.2% of children aged up to 4 years start to stutter (Reilly et al., 2013; Yairi & Ambrose, 2013). About 75% from them recover with or without treatment in the first years after stuttering onset (Yairi & Ambrose, 1999). Reilly et al. (2013), Yairi and Ambrose (1999) and recently Carey et al. (2020), however, reported only 6%, to 9% recovery during the first year after stuttering onset, about half of them with the help from a stuttering specialist. Given the lack of concrete data, we need to estimate, based on numbers from the literature. We estimate that about one third of the preschool

age children who start to stutter, seek treatment. That is, 2.6% - 3.7% of children between 2.5 and 6.5 years of age.

The number of interventions performed per year in Belgium is estimated as to our knowledge, there is no access to data about the number of interventions for stuttering with preschool age children in Belgium. In Flanders (Statistiek Vlaanderen, 2020), 263 517 children attend preschool; In Wallonia and Brussels, 187 791 (La FWB en chiffres, 2018, p. 124). Based on our own calculations, we estimate that about 45 130 children start to stutter, and about 1354 children of these children seek treatment for stuttering (10% incidence, 3% seeking treatment).

